### Study outcomes and data analyses

#### Summative evaluation

Our four major research questions for this project are illustrated above.

We will use a linear mixed model (LMM) for the primary outcomes weight loss (kilogram) and fitness (BSA-Score), and for the outcome smoking cessation, we use a generalized linear model (GLMM) because of the dichotomous outcome variable (Smoking yes/no). The cluster variable is the person-id (level 2-group variable) with the time point nested within it (level 1 measurement), that permits us to model individual and group level changes [23–25]. For each primary outcome, we apply the following basic model with cross-level interaction and random slopes:

Level 1: *Outcome* = *β*_0*j*_ + *β*_1*j*_ ∗ *time* + *β*_*nj*_ ∗ *X*_*nj*_ + *r*_*ij*_

Level 2: *β*_0*j*_ = *γ*_00_ + *γ*_01_ ∗ *group* + *γ*_0*n*_ ∗ *Z*_0*n*_ + *u*_*oj*_
$$ {\beta}_{1j}={\gamma}_{10}+{\gamma}_{11}\ast group+{u}_{1j} $$

“Group” will be a dichotomous variable, which contrasts the intervention group vs. the control group. ’Time’ consists of four time points coded with 0 to 3.

Possible covariates (see Table 4) will enter the model at level 1 (X) when they are measured at more than one time point or at level 2 (Z) when they are only measured at baseline. The covariates differ in type and number between the three coaches. The components X and Z are therefore only placeholders. The covariates considered may represent real-life conditions of participants existing independently of the program; they can be beneficial or detrimental to participants’ goal attainment or outcomes. The social environment in particular may be conducive or an obstacle [26–30]. The importance of social and emotional support from people, who are close, is also pointed out by the NICE guideline *Behaviour Change: individual approaches* [31]. Tiredness and a decrease in drive and activity are indications of mood disorders. Self-efficacy, motivation and intention to change, as well as functional or physical limitations are predictors for behavioral change and associated with mental health, health status, and comorbidities [32–40]. Furthermore, it is likely that additional addictive behaviors and low degree of mental health will make smoking cessation more difficult [33, 41, 42]. Since past behavior predicts future behavior, as confirmed in a meta-analysis [43], preconditions such as mental health, health status comorbidity, additional addictive behavior, but also social support, assessed at baseline, are considered as program-independent covariates of primary outcomes. We use these covariates, along with sex, age, and primary outcome at baseline to adjust the statistical models in the analyses. In these models, coefficient *γ*_10_ refers to the change over time of the intervention groups (hypothesis 1), while coefficient *γ*_11_ refers to the difference in change between intervention and control group (hypothesis 2).

For the analyses of secondary outcomes, measuring mean changes over time (see Table 3), we use linear mixed models analogous to the primary outcomes in weight loss and fitness. Differences between intervention and control groups in for example “Health related goal intention” or “Perceived goal attainment” will be analyzed using *t* tests.

To test the dose-effect association (hypothesis 3), the outlined model will be adapted—here, we only use the intervention group, so the group variable will be dropped. Instead of the group variable, a variable that code the use (e.g., number of logins) of the coach will enter the model at level 2.

All metric covariates at level 1 will be group mean-centered, while metric covariates at level 2 will be grand mean-centered. Categorical variables enter as dummy-coded (0/1) variables.

Post-hoc analyses with correction for multiple testing will be conducted to identify changes between specific time points to analyze short-term effects, e.g., between t0 and t1. As effect size, with their 95% confidence intervals, we will calculate Cohen’s *d* bases on the *t* values from the pairwise comparisons from the LMM respective odds ratio for the GLMM.

In the case of the *SmokingCessationCoaching*, we will drop the baseline (T0) from the model, because every case concerns smoking. It is, therefore, not possible to calculate the odds ratio for the change between baseline and post-intervention. Instead, we will use the difference in smoking cessation at post intervention between both groups as the effect size.

Furthermore, we will apply structural equation modeling to test various models for assessing potential mediators of the intervention effect on outcomes.

The analyses are carried out according to the intention-to-treat principle (ITT). In ITT, all randomized participants will be considered in the main analyses. In per-protocol analyses (PP), only those participants will be included who have been randomized, have participated at all time points, and filled out corresponding primary outcomes. The randomization condition for study participants was that they accessed the program at least once.

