*Smoking Cessation*: 4 months after completing the program*Increasing Fitness* and *Losing and Maintaining Weight*: 6 months after completing the programFollow-up t3: 12 months after completing the program in all three RCTs.

The data on program usage will be recorded during the entire study period.

In the RCT *Smoking Cessation* qualitative telephone interviews will be carried out once the t1 questionnaires have been completed.

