### Research questions and hypothesis

The following questions and hypotheses are being investigated in this study
What effects do the online programs within the three health goals *Losing and Maintaining Weight*, *Increasing Fitness*, and *Smoking Cessation* have on the primary and secondary outcomes variables reported by participants?We assume that we will observe statistically significant improvements with small to medium effect sizes for each program.Will the intervention groups (interactive health programs) in each RCT reveal stronger effects on primary and secondary outcomes in comparison to the control groups (non-interactive health programs)? We will test the hypothesis that the intervention groups’ changes in the primary and secondary outcomes are more positive than the control groups’. Our focus is on long-term effects so we will analyze the change between baseline (t0) and 1 year after the intervention finishes (t3), while short-term effects are part of the secondary analyses. We expect small to medium effect sizes from the comparison between these two groups.Does the intensity of use of health programs have an impact on their effects?The hypothesis we test is that study participants who use their health program more frequently and intensively achieve better outcomes than study participants who use the program less often or less intensively.How satisfied with the programs offered are the study participants in the intervention- and control groups? This question will be examined exploratively in secondary analyses.

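### The coefficient that tests hypothesis 2 is a difference in average slope, not the difference in change from t0 to t3 that the hypothesis targets

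*Protocol article*

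**What the plan says.** Under Research questions and hypothesis, the article sets the target of the between-arm comparison: "Our focus is on long-term effects so we will analyze the change between baseline (t0) and 1 year after the intervention finishes (t3"). Short-term effects are placed among the secondary analyses.

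Under Summative evaluation it states for the primary outcomes: "we apply the following basic model with cross-level interaction and random slopes". The printed equations contain one time coefficient per person, made up of γ10, γ11 × group and a random deviation. Time "consists of four time points coded with 0 to 3". The coefficient γ11 "refers to the difference in change between intervention and control group (hypothesis 2"), and γ10 "refers to the change over time of the intervention groups (hypothesis 1").

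The same section adds three things:
- Post-hoc comparisons between specific time points, corrected for multiplicity, to study short-term effects.
- Cohen's d taken from pairwise comparisons within the linear mixed model.
- For smoking, removal of t0 from the model, with the post-intervention difference between arms as the effect size.

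**The concern.** A model with one linear time term has one group-by-time coefficient, and that coefficient compares average slopes across all four visits. It equals one third of the t0-to-t3 difference in change only if the arm difference follows a particular shape. The test named for hypothesis 2 can therefore answer a different question from the one the hypothesis asks.

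The likely direction of error matters here. If the arms differ most at the end of the program and converge later, the slope understates the long-term benefit. Convergence is conceivable, because the Control groups section gives every participant the interactive coach once the trial program ends. The article does not predict this course, however, and the Intervention groups section describes tools meant to prevent relapse.

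At stake are the primary estimate for weight and fitness, the power for the fitness outcome, and, in the smoking trial, whether the named coefficient can detect a benefit at all.

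**Working it through.** **The plan's own figure.** Table 5 assumes an effect size of 0.25, two-sided alpha 0.05 and 80% power. The two-sample t-test needs 252.1, so 253 per arm. With 50% dropout this is 506 per arm, and 1,012 × 1.1 = 1,113.2, so 1,114. The figure reproduces, but for a simple two-group comparison rather than for γ11.

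**What γ11 estimates.** For codes 0, 1, 2, 3 the least-squares slope weights are −0.3, −0.1, 0.1, 0.3. With complete data, no covariates, and a random intercept and slope on the same codes, the mixed model gives the same weights (checked numerically for two covariance settings). Let d1, d2, d3 be the arm differences at t1 to t3, with d0 = 0 by randomization. The implied t0-to-t3 effect is

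3 × γ11 = 0.9 × d3 + 0.3 × (d2 − d1), whereas the target is d3.

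**Power.** Assume equal correlations ρ between visits, and an effect of 0.25 in SDs of the t0-to-t3 change. The change has variance 2(1 − ρ) and 3 × γ11 has variance 9 × 0.2 × (1 − ρ) = 1.8(1 − ρ). The ratio of SDs is √0.9 = 0.949 for any ρ. With e = 3 × γ11 when d3 = 1, power = Φ(0.25 × e / 0.949 × √(253/2) − 1.96).

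| Assumed profile (d1, d2, d3) | 3 × γ11 | Target | Power of γ11 |
|---|---|---|---|
| Linear in the codes (1/3, 2/3, 1) | 1.00 | 1 | 0.84 |
| Immediate and sustained (1, 1, 1) | 0.90 | 1 | 0.76 |
| Half the t1 gain kept (2, 1.5, 1) | 0.75 | 1 | 0.60 |
| A quarter kept (4, 2, 1) | 0.30 | 1 | 0.14 |

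The t0-to-t3 contrast has power 0.80 in every row. For weight itself Table 5 assumes 0.50. Replacing 0.25 by 0.50, γ11 keeps power 0.99 when half the gain is kept and 0.43 when a quarter is kept. For weight the milder profiles therefore distort the estimate more than the power.

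**Gain fully lost by t3.** Weight differences of −2, −1, 0 kg give 0.9 × 0 + 0.3 × (−1 + 2) = +0.3 kg, a spurious effect in favour of control where the target is zero.

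**Sign reversal.** With benefit counted as positive, 3 × γ11 < 0 exactly when d1 > d2 + 3 × d3. If d2 is at least d3, less than 25% of the t1 gain must remain. Example: benefits of 3, 1.5 and 0.4 kg give 0.36 + 0.45 − 0.90 = −0.09 kg.

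**Visit spacing.** For weight and fitness the visits fall at about 0, 2.8, 8.8 and 14.8 months. A difference linear in real months gives 3 × γ11 = 1.02 for a target of 1, so spacing adds almost nothing. Linear time in months has t0-to-t3 weights −0.75, −0.43, 0.25, 0.93. The profile (4, 2, 1) then gives −0.30 instead of +0.30, which is further from the target.

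**Dropout.** In one assumed monotone pattern (20% lost after t0, 15% after t1, 15% after t2, the same in both arms), a fit without imputation gives weights −1.06, −0.13, 0.45, 0.75. Half the gain kept then gives −0.26 + 0.67 + 0.75 = 1.15 rather than 0.75. The size and direction of the error thus depend on attrition as well as on the trajectory.

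**Smoking.** On t1 to t3 the slope weights are −0.5, 0, 0.5. A constant 15% against 2% (the Table 5 rates) has odds ratio (0.15/0.85)/(0.02/0.98) = 8.6 at each visit, log 2.157, so γ11 = 0. With 30%, 20%, 15% against 2%, the log odds ratios are 3.045, 2.506, 2.157 and γ11 = (2.157 − 3.045)/2 = −0.44, although the intervention is better at every visit. This arithmetic uses marginal log odds.

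**The case against.** The strongest reply is that the article does not settle that time is linear. Codes 0 to 3 could label factor levels, "Categorical variables enter as dummy-coded (0/1) variables", and Cohen's d is to come from pairwise comparisons, which a single slope cannot supply as separate visit contrasts. A t0-to-t3 comparison may therefore be intended. What stands is that the sections are inconsistent with each other. Factor coding, however, would need three time coefficients and three interactions, while the equations show one of each and hypothesis 2 is tied to that one interaction. The pairwise comparisons are called post hoc and directed at short-term effects. The text does not confine them to such effects, but nowhere makes one of them the test of hypothesis 2.

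A second reply is that the trajectories are assumed. That is correct: a sustained gain costs only 10%, and a difference linear in the codes costs nothing and gains power.

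A reader might infer more than the document supports:
- That unequal visit spacing is the cause and real months the cure. The single slope is the cause, and recoding to months can make matters worse.
- That the sign will reverse. This needs strong relapse; a profile ending at zero gives a spurious effect, not a reversal.
- That γ10 is the control arm's slope. The article does not say which arm is coded 0. If the intervention arm is, its description of γ10 is correct. Either way γ10 covers one arm only, while hypothesis 1 concerns every program.

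**Conclusion.** The point holds for weight and fitness: the stated test of hypothesis 2 does not estimate the stated target unless the arm difference has a convenient shape. With complete data the error runs from nil, through 10% and 25% attenuation, to a spurious effect when the gain is lost by t3, and to reversal only under the condition shown. The power loss is from 0.80 to about 0.76 or 0.60 for an effect of 0.25, and γ11 has the higher power (0.84) if the difference is linear in the codes.

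These sizes rest on assumed trajectories, equal correlations between visits and no covariates. The complete-data weights are relevant to the intention-to-treat analysis as far as outcomes are imputed, as Sensitivity analysis and missing values plans when missingness at random holds; without imputation, dropout changes them. For smoking the mismatch needs no trajectory assumption: with t0 removed, γ11 cannot be a change from t0, and a constant benefit gives zero. The mismatch between target and test should be resolved before the analysis.

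**What to change.** - **Weight and fitness.** Enter time as a categorical factor and pre-specify the group-by-t3 contrast, the between-arm difference in change from t0 to t3, as the primary test of hypothesis 2. Keep the t1 and t2 contrasts as secondary. Take Cohen's d for the primary result from the same contrast. Do not rely on recoding time to months.
- **Smoking.** State that γ11 does not test hypothesis 2, and name the between-arm difference in abstinence at t3 as the primary test.
- **Hypothesis 1.** State which arm is coded 0, and estimate each arm's own t0-to-t3 change for weight and fitness: the time effect for the reference arm, and time effect plus interaction for the other.
- **Text.** Bring Research questions and hypothesis and Summative evaluation into line with this.

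The cost is wording and two extra time parameters per arm. If the difference really is linear in the codes, power falls from 0.84 to 0.80, which is the planned level. The sample size need not change.

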**Confounder**							
Mental illness	Patient Health Questionnaire (PHQ-2 [62])/mean score One self-developed item/dichotomous	W, F, S	3	**x**	**x**	**x**	**x**
Health impairments	Comorbidity Score (KoMo) [32]/mean score	W, F, S	24	**x**			
General state of health	BRAHMS [50]; adapted	W, F, S	1	**x**			
Addictive substances other than tobacco (s)	Alcohol, Smoking and Substance Involvement Screening Test (WHO-ASSIST), question N°2 [63] ; three of ten items: alcohol, cannabis, sedatives and sleeping pills/value of each Item	S	3	**x**	**x**	**x**	**x**
Social support	The weigh-related interactions Scale (WRIS) [26]; adapted/mean score	W	14	**x**	**x**	**x**	**x**
	Social support [64] (in prep.)/mean score	F	12	**x**	**x**	**x**	**x**
	Partner Interaction Questionnaire (PIQ-20 [65]); adapted/mean score	S	17	**x**	**x**	**x**	**x**

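### The covariate rule for the primary model contradicts itself; followed as written, it conditions the group-by-time effect on values measured after randomization

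*Protocol article*

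**What the plan says.** The Summative evaluation section gives one model form: "For each primary outcome, we apply the following basic model with cross-level interaction and random slopes". Level 1 holds time and a set of covariates X. Level 2 holds group and a set of covariates Z. The cluster (level-2 unit) is the person. γ11, the effect of group on the time slope, is named as the test of hypothesis 2.

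The rule for filling X is "Possible covariates (see Table 4) will enter the model at level 1 (X) when they are measured at more than one time point"; covariates measured only at baseline go to Z. On centering, the section states: "All metric covariates at level 1 will be group mean-centered, while metric covariates at level 2 will be grand mean-centered".

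The Confounder block of Table 4 marks these at all four time points:
- mental illness, all three RCTs: "Patient Health Questionnaire (PHQ-2 [62])/mean score One self-developed item/dichotomous"
- social support, all three RCTs, each with its own scale; for smoking, "Partner Interaction Questionnaire (PIQ-20 [65]); adapted/mean score"
- other addictive substances, smoking RCT only: "three of ten items: alcohol, cannabis, sedatives and sleeping pills/value of each Item"

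Comorbidity and general state of health are marked at t0 only.

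Later in the same paragraph as the level-1 rule, mental health, health status, comorbidity, additional addictive behavior and "also social support, assessed at baseline, are considered as program-independent covariates of primary outcomes". These covariates, with sex, age and the baseline outcome, are then named as the adjustment set.

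**The concern.** Two analysts could each follow this section and fit different primary models. One would use the t0 values of PHQ-2, social support and substance use. The other would use their t0 to t3 values as time-varying terms.

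The second model conditions on variables measured after allocation. The intervention could change them: the protocol describes technically guided psychological input in all coaches, barrier management in the fitness and smoking coaches, and mindfulness modules and telephone counseling in the smoking coach. The outcome could change them too, for example if weight loss or quitting alters mood or the support received. Adjusting for them removes whatever part of the effect runs through them. It can also create a spurious association if an unmeasured time-varying factor drives both covariate and outcome. γ11 would then not be the total effect of being randomized to the interactive program.

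Person-mean centering adds to this. It strips out the stable differences between people, which are the stated reason for adjusting, and keeps only within-person change.

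**Working it through.** **1. Which level do the covariates take?** PHQ-2, social support and (smoking) other substances are measured at t0, t1, t2 and t3, which is more than one time point, so the rule sends them to level 1.

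**2. Could level-1 X still mean the baseline value?** No. A baseline value x repeated at four time points has person mean x, and x − x = 0 for everyone. Under the centering rule a metric level-1 covariate carries information only if it varies over time. So the level-1 rule and the baseline description cannot both apply to the same variable.

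**3. The plan's own sample size (Sample size calculation, Table 5).** Fitness: d = 0.25, two-sided alpha 0.05, power 0.80. The two-sample t test needs 252.1 per arm, rounded up to 253. With 50% dropout, 253 / 0.5 = 506. Then 2 × 506 × 1.1 = 1113.2, against 1,114 stated. The figure is reproduced; power at 253 per arm is 0.80. No stated figure is disputed.

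**4. Size of the distortion, fitness RCT only.** Let a be the program's effect on the covariate by t3 (in SD) and b the covariate's effect on the outcome. Neither is in the documents; both are assumptions. With no other shared cause, the adjusted effect is

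d_adj = d − a × b.

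A simulation (four time points, person-mean-centered covariate, group-by-time slope, true total effect 0.25) agrees. Power is for the two-sample t test at 253 per arm with SD held at 1.

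| a | b | d − a×b | simulated | power |
|---|---|---|---|---|
| 0 | 0.3 | 0.250 | 0.25 | 80% |
| 0.10 | 0.3 | 0.220 | 0.22 | 70% |
| 0.25 | 0.3 | 0.175 | 0.17 | 50% |
| 0.40 | 0.3 | 0.130 | 0.13 | 31% |
| 0.25 | 0.5 | 0.125 | 0.125 | 29% |
| −0.25 | 0.3 | 0.325 | 0.33 | inflated effect |

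With a = 0.25, no causal path (b = 0) and a shared time-varying cause of covariate and outcome, the simulated adjusted effect was 0.19.

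**5. Does baseline adjustment avoid this?** In one simulated data set (2,500 per arm, true effect 0.25, a = 0.25, b = 0.5), a mixed model with random slope gave, for the t0 to t3 difference:
- no covariate: 0.259 (SE 0.023)
- t0 covariate only: 0.259 (SE 0.023)
- centered time-varying covariate: 0.121 (SE 0.019)

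The time-varying covariate lowered the standard error somewhat. The power column ignores that gain, so it somewhat overstates the loss.

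**6. The other two RCTs.** For weight, Table 5 assumes d = 0.50; the 253 per arm comes from physical activity as a key secondary outcome (Table 5, footnote 3). Taking off the largest product in the table, 0.50 − 0.125 = 0.375, leaves power of about 99% at 253 per arm. The smoking outcome is binary and uses a GLMM, which was not simulated.

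**The case against.** The wording is tentative. The section speaks of possible covariates and calls X and Z placeholders, and the sentence naming the adjustment set speaks of baseline assessment. A reader might therefore hold that baseline adjustment is what is meant. It may be, but the placeholder remark leaves open which covariates enter, not at which level, and the centering rule makes sense only for time-varying terms. The contradiction stands. So does the converse: it is not established that post-randomization values will be used.

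The Sensitivity analysis section plans linear mixed models without covariates, which would show the unadjusted group-by-time effect for weight and fitness. This softens the problem. It does not remove it: those models are listed as sensitivity analyses, and as linear models they do not clearly cover the smoking GLMM.

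The assumed shifts may be generous. Participants are described as healthy, the control arm also receives a program, and 0.25 SD on mood or support would equal the whole planned effect on physical activity. That is a fair limit on the size; at a = 0.10 the loss is modest.

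A reader might infer that the plan is bound to remove part of the intervention effect, or that all three trials lose power. The documents support neither. They give no covariate shifts, the direction can go either way, and the power figures belong to fitness alone. Nor do the documents show that imputing these covariates adds harm: multiple imputation of predictors and outcomes is already planned for the intention-to-treat analysis.

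**Conclusion.** The section contradicts itself on how repeatedly measured Table 4 covariates enter the primary model, and this should be settled before analysis. If the level-1 rule governs, γ11 estimates an effect conditional on post-randomization variables, not the total randomized effect of hypothesis 2. That change of estimand follows from the text; the size of any bias does not. The bias is absent when the program leaves the covariates unchanged and no shared cause exists. For fitness, under the assumed favorable shifts that were run, the effect falls from 0.25 to between about 0.22 and 0.125, and power from 80% to between about 70% and 29%; under the unfavorable shift it rises to about 0.33. Weight would keep high power, though its estimate could still be biased. No figure is offered for smoking.

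**What to change.** In the primary intention-to-treat models for all three RCTs, enter only the t0 value of each Table 4 covariate, at level 2, with metric ones grand-mean centered. Delete the level-1 X term and the centering rule for it. State that t1 to t3 values of PHQ-2, social support and other substance use are reserved for the structural equation models of mediation that the protocol already plans. The baseline values are already collected, so the cost is a change of analysis wording, and the planned sample size stands.

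### In the weight and fitness mixed models the t0 outcome is both a response and a covariate, which leaves the group-by-time effect unadjusted for baseline and overstates its standard error

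*Protocol article*

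**What the plan says.** All of this is in the protocol article. Under Summative evaluation, weight and the physical activity score are analyzed with a linear mixed model, described as a "basic model with cross-level interaction and random slopes", in which time "consists of four time points coded with 0 to 3". The level-2 equation for the intercept contains group, the covariates Z and a random term. The equation for the slope contains only group and a random term.

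Covariates enter "at level 2 (Z) when they are only measured at baseline". The baseline primary outcome is named outright as one of them: "We use these covariates, along with sex, age, and primary outcome at baseline to adjust the statistical models in the analyses". The treatment effect is γ₁₁, which "refers to the difference in change between intervention and control group (hypothesis 2". Research questions and hypothesis gives the matching contrast: "we will analyze the change between baseline (t0) and 1 year after the intervention finishes (t3".

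The baseline row is removed in one trial only, smoking: "we will drop the baseline (T0) from the model, because every case concerns smoking".

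Sensitivity analysis and missing values adds a mixed model without covariates for comparison, and has missing outcomes imputed in the intention-to-treat analysis.

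**The concern.** A baseline value can serve as a response or as a covariate in a longitudinal model, but not as both in one equation. Here a single coefficient has to fit t0 (where the right value is 1, since the value predicts itself) and also t1 to t3 (where it is the correlation with baseline). No single value fits both, and the variance components absorb the misfit.

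Two things are at stake for the main test of hypothesis 2 in two of the three trials. The article motivates the adjustment by the predictive value of past behavior, yet the tested coefficient would not receive it. Its standard error would also be wrong in the direction that costs power.

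**Working it through.** **Inputs from the article.** Times 0, 1, 2, 3; random intercept and slope; baseline outcome in the intercept equation only; two-sided α 0.05; power 0.80; effect 0.25 for fitness and 0.50 for weight; 253 per arm evaluable (Table 5).

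**The plan's own figure.** n = 2(1.96 + 0.8416)²/0.25² = 251.2, or 252 by the normal approximation; the t-test calculation gives 252.1, rounded up to 253. With 50% dropout this is 506 per arm, and 1012 × 1.1 = 1113.2, rounded up to 1114. These reproduce and are not in dispute.

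**Assumed, because the article gives no covariance.** Outcome variance 1 with compound symmetry (correlation r) as the worked case, and other structures for the range.

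**Step 1: the estimate does not change.** With balanced data the model's slope estimate weights the four times by (t − 1.5)/5 = (−0.3, −0.1, 0.1, 0.3). Entering baseline with coefficient b replaces each Y_t by Y_t − bY₀. The weights sum to zero, so the term in b vanishes for any b. The estimate of γ₁₁ is identical with and without the covariate.

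**Step 2: the variance components.** Maximum-likelihood fit of the stated model at population level, r = 0.6:

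| | no baseline covariate | with baseline covariate |
|---|---|---|
| baseline coefficient | none | 0.790 |
| random-intercept variance | 0.60 | 0.007 |
| random-slope variance | 0 | 0.0413 |
| residual variance | 0.40 | 0.317 |

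The misfit at t0 reappears as slope variance that does not exist in the data.

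**Step 3: the standard error.** SE(3γ₁₁) = 3√[(2/253)(slope variance + residual variance/5)].
- Without the covariate: 3√[(2/253)(0 + 0.0800)] = 0.0754, which is also the true SD of the estimate.
- With it: 3√[(2/253)(0.0413 + 0.0634)] = 0.0863, a ratio of 1.144.

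**Step 4: power.** A sustained effect of 0.25 SD at t1 to t3 gives 3γ₁₁ = 3 × 0.25 × (−0.1 + 0.1 + 0.3) = 0.225.
- Without the covariate: Φ(0.225/0.0754 − 1.96) = 85%.
- With it: Φ(0.225/0.0863 − 1.96) = 74%.
- For the weight trial's assumed 0.50, 3γ₁₁ = 0.45 and Φ(0.45/0.0863 − 1.96) is still above 99.9%.

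**Step 5: range over assumed structures** (SE of γ₁₁ per time step, 253 per arm).

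| Structure | no covariate (true SD) | with covariate | excess |
|---|---|---|---|
| weight-like (variances: intercept 0.90, slope 0.0144, residual 0.0144) | 0.01169 | 0.01194 | 2% |
| autoregressive 0.8 | 0.02963 | 0.03067 | 4% |
| autoregressive 0.6 | 0.03750 | 0.03906 | 4% |
| activity-like (0.49, 0.0225, 0.49) | 0.03086 | 0.03432 | 11% |
| compound symmetry 0.5 | 0.02812 | 0.03196 | 14% |
| compound symmetry 0.8 | 0.01778 | 0.02055 | 16% |

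Over ten structures the range was 2% to 16%. For a test that would have 80% power, Φ(2.80 − 1.96 × ratio) gives about 79% down to 70%. The true two-sided α, 2[1 − Φ(1.96 × ratio)], is about 0.046 down to 0.024.

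**Step 6: checks.** In 200 simulated trials per structure the mean model SE rose from 0.01164 to 0.01190 (weight-like), 0.03085 to 0.03431 (activity-like) and 0.01794 to 0.02052 (compound symmetry 0.8). Power fell from 0.745 to 0.735, 0.785 to 0.715 and 0.825 to 0.72. With 506 per arm, an assumed 50% dropout completely at random and no imputation, the model SE was 4% to 18% larger than without the covariate. In that case the estimate is no longer exactly identical, but it is still not baseline-adjusted.

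**The case against.** The best defense is that little harm follows. The error is conservative and does not bias γ₁₁ on average, so it cannot produce excess false positives. The weight trial was sized on its secondary outcome and has power to spare. The planned model without covariates has a correctly calibrated standard error. All of that stands. But that model is a sensitivity analysis, and it is not baseline-adjusted either. As far as this covariate is concerned, it would also return the same estimate with a smaller standard error, so the two analyses could differ in significance for no substantive reason.

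It might be said that t1 to t3 are the intended response. The text does not allow this: the t0 row is dropped for smoking alone, and comparisons of t0 with t1 are planned. Nor does moving the covariate to level 1 help, because centering within person turns a constant into zero.

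A reader might infer more than the article supports:
- **That the covariate causes chance imbalance to carry into γ₁₁.** With no effect and a 0.15 SD imbalance at r = 0.6, 3γ₁₁ is 3(−0.3 × 0.15 + 0.3 × 0.09) = −0.054 SD, but this is the same with and without the covariate. It belongs to the declared change contrast. With 557 per arm such an imbalance is also unlikely: 0.15/√(2/557) = 2.5 standard errors.
- **That the loss should be measured against an analysis of covariance at t3** (SE 0.071, power about 94% at r = 0.6). Part of that gap comes from the linear time coding, which turns 0.250 into 0.225, and not from the double use of baseline.
- **That the smoking model has the same fault.** Its t0 row is dropped, and the article says that covariates differ between the programs. A constant would simply not be entered.
- **That t tests for goal intention are an error.** The sentence beginning "Differences between intervention and control groups in for example" does not say whether follow-up values or changes are compared, and a t test between randomized arms is valid.

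**Conclusion.** The point holds for the weight and fitness mixed models. As specified, the baseline outcome does not adjust γ₁₁, removes the random intercept and overstates the standard error of γ₁₁.

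That the estimate does not change is algebra and needs only balanced or imputed data. The size of the excess rests on assumed covariances: about 2% to 16%, smallest in the strongly tracking weight-like structure. It also needs the random slope that the article specifies; with a random intercept alone the standard error would not change. The fall from 85% to 74% is for one structure toward the upper end of that range and should be quoted with its assumptions.

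The practical cost is lost power, mainly in the fitness trial, where 253 per arm was set for 80% power at an effect of 0.25.

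**What to change.** Before the t3 analysis, state one of two models for weight and fitness:

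- **(a)** Take t1, t2 and t3 as the response, with the baseline outcome and baseline-by-time as covariates, and report the group difference at t3.
- **(b)** Keep t0 as a response, constrain the arms to a common mean at t0, and remove the baseline outcome from the covariates.

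Either one gives the baseline adjustment that the article intends. Under (b) with linear time, the standard error of γ₁₁ in the structures above would be 0.01168 (weight-like), 0.02734 (activity-like), 0.02411 (compound symmetry 0.5) and 0.01691 (compound symmetry 0.8), in each case no larger than that of the model without the covariate. If (a) is chosen, the comparison of t0 with t1 should be reworded as a baseline-adjusted group difference at t1.

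The cost is a change of wording. All the baseline values are already collected, and neither the sample size nor the schedule changes.
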